[figure not shown]

## GLOSSARY OF ABBREVIATIONS

|           |                                                                    |
|-----------|--------------------------------------------------------------------|
| AE        | adverse event                                                      |
| ALT (GPT) | alanine aminotransferase                                           |
| AST (GOT) | aspartate aminotransferase                                         |
| AMG       | Arzneimittelgesetz                                                 |
| BP        | blood pressure                                                     |
| CRF       | case report form(s)                                                |
| EMA       | European Medicines Agency                                          |
| ECG       | electrocardiogram                                                  |
| EVR       | early virological response                                         |
| FDA       | Food and Drug Administration                                       |
| FU        | Follow-up visit                                                    |
| GCP       | Good Clinical Practice                                             |
| HAV       | hepatitis A virus                                                  |
| HBV       | hepatitis B virus                                                  |
| HCV       | hepatitis C virus                                                  |
| HIV       | human immunodeficiency virus                                       |
| ICH-GCP   | International Conference of Harmonisation - Good Clinical Practice |
| IEC       | Independent Ethics Committee                                       |
| IFN       | interferon alpha                                                   |
| INR       | international normalised ratio                                     |
| ITT       | intention to treat                                                 |
| IU        | international units                                                |
| IUD       | intrauterine device                                                |
| LKP       | Leiter der klinischen Prüfung (Coordinating Investigator)          |
| MEDRA     | Medical Dictionary for Regulatory Activities Terminology           |
| NYHA      | New York Heart Association                                         |
| PEG       | polyethylene glycol                                                |

# 1 BACKGROUND AND RATIONALE

## 1.1 *Chronic Hepatitis C*

More than 120 million people world-wide are chronically infected with the hepatitis C virus (HCV) , a RNA virus belonging to the family flaviviridae which was discovered in 1989 . HCV is transmitted primarily through exposure to blood products and intravenous drug use. 50-90% of patients with acute HCV infection develop a persistent infection. Heterogeneity is high, there are 6 HCV-genotypes and more than 90 subtypes. The chronic sequelae of chronic HCV infection are liver fibrosis, cirrhosis, and hepatocellular carcinoma . In addition to liver disease, HCV infection has been associated with a wide variety of extrahepatic manifestations such as mixed cryoglobulinaemia, membranoproliferative glomerulonephritis and porphyria cutanea tarda .

Measures to prevent HCV infection such as blood screening programs led to a decline in HCV incidence in the developed world. However, despite prevention measures, we still anticipate an increasing number of patients with sequelae of HCV infection in the following 10-20 years .

During the last 15 years there has been an enormous achievement in the diagnosis, management, and therapy of hepatitis C. Analysis of HCV-genotypes, quantification of HCV-RNA viral load, and calculation of viral kinetics allow better management of patients with chronic hepatitis C. Current standard treatment of HCV with pegylated interferon alpha (PEG-IFN) and ribavirin has been optimized and the first direct antiviral drugs are in development and may lead to chance to cure chronic hepatitis C in the majority of cases .

## 1.2 *Study drugs – Current standard treatment*

### **Pegylated Interferon alpha-2b (PegIntron®)**

Before the identification of the Hepatitis C Virus (HCV) as the infectious agent for non-A, non-B hepatitis it turned out that Interferon alpha (IFN) may lead to normalization of transaminases and improvement of liver histology . Due to the identification of HCV it became possible to measure the success of therapy as a long lasting disappearance of HCV-RNA from serum, a so-called sustained virological response (SVR). Since that time the SVR rate has increased from 5-20% with an IFN monotherapy to 40%-50% with the combination of IFN and ribavirin (11;12). The development of pegylated interferon alpha (PEG-IFN) added a new milestone to the treatment of chronic hepatitis C. Pegylation of the IFN allows a once weekly administration due to an improved pharmacokinetic profile. PEG-IFN/ribavirin combination therapy improved the overall SVR to 54-63% .

PEG-IFN alpha-2b is given as a subcutaneous injection adjusted for body weight (1.5 µg/kg once weekly). Side effects of PEG-IFN alpha-2b include fatigue, flu-like symptoms, neuropsychiatric symptoms, autoimmune phenomena, and haematological abnormalities which may lead to dose modifications or therapy discontinuation. PegIntron® was approved by the EMEA in 2002 for the treatment of chronic hepatitis C.

### **Ribavirin (Rebetol®)**

Ribavirin should be administered according to the bodyweight of the patient. A retrospective analysis of the large PEG-IFN alpha-2b/ribavirin pivotal trial revealed that the optimal ribavirin dose is at least 10.6 mg/kg . Therefore ribavirin (Rebetol®) is recommended at a concentration of approximately 11 mg/kg body weight in combination with PEG-IFN alpha-2b (see dosing). The main side effect of ribavirin is a dose dependent haemolysis which may require dose modification. Rebetol® was approved by the EMEA in 1999 for the treatment of chronic hepatitis C.

The current standard treatment duration is dependent on the HCV-genotype. Patients with the HCV-genotype 1 are treated for 48 weeks and patients with the HCV-genotypes 2 and 3 are treated only for 24 weeks.

### **1.3 Rationale for the Study**

The main discussion within the scientific community is to optimize the current standard treatment of chronic hepatitis C (CHC) to improve the response rates, in particular the treatment duration. There are two different concepts to optimize the treatment duration. While some patients may be treated for a shorter period of time to reduce costs and side-effects, others may need longer treatment to improve the response rates.

Many studies have been investigating reductions in treatment duration for HCV-genotypes 2 and 3 to 16, 14, or even 12 weeks. The first reported results are promising, but it turns out that individual factors need to be considered when treating patients for less than 24 weeks. The rapid virological response (RVR) after 4 weeks of therapy (HCV-RNA negative in the serum at treatment week (TW) 4) is one of the critical factors that are associated with the success of a shorter therapy. Only patients who showed RVR at week 4 had high SVR rates after 16 weeks, 14 weeks, or even after 12 weeks of therapy, whereas those without RVR had lower response rates, even with the 24-week schedule. In addition to the RVR other factors are associated with the response in patients with HCV-genotypes 2 and 3. These are the baseline viral load and the presence of liver cirrhosis. In conclusion, patients with HCV-genotype 2 and 3 and low viral load who have a RVR after 4 weeks of therapy can be treated for less than 24 weeks and patients without RVR (especially HCV-genotype 3 and high viral load) may be treated even for more than 24 weeks. However, the optimal treatment duration for patients without RVR is not known until now.

In this study we intend to treat patients with chronic hepatitis C of genotype 2 or 3 having characteristics associated with poor treatment response for additional 12 or 24 weeks beyond the standard treatment of PEG-IFN alpha-2b plus ribavirin.

## **2 OBJECTIVES**

The objective of this study is to compare the efficacy of a treatment extension of 12 versus 24 weeks in patients with HCV-genotypes 2 and 3 who are treated with 1.5 µg/kg PEG-IFN alpha-2b and 800-1400 mg ribavirin (standard dose) for 24 weeks (standard duration) and who are not HCV-RNA negative (< 15 IU/ml) after 4 weeks of standard treatment

## **3 STUDY DESIGN**

### **3.1 Overview of Study Design**

This is a German open label multi center randomized phase IV trial to assess the efficacy of 12 versus 24 weeks of extended treatment in HCV-G2/3 patients with an ongoing standard treatment with PEG-IFN alpha-2b and ribavirin.

150 patients shall be enrolled. Estimated study start will be July 1st 2008; period for recruiting is planned to be 18 months. The recruitment period will be extended until December 31st 2012 and last follow up visit will be performed in June 2013.

Approximately 30 centers specialised in the treatment of hepatitis C will take part in the study. The number of patients per center is planned to be at least 3.

Patients with HCV-genotype 2 and 3 are eligible if they are non rapid virological responders (HCV-RNA positive after 4 weeks of treatment).

**Group A:** PegIntron® 1.5 µg/kg once weekly (QW) subcutaneous (sc) plus Rebetol® 800-1400 mg per os divided in 2 daily doses for additional 24 weeks beyond standard treatment with 24 weeks follow-up

**Group B:** PegIntron® 1.5 µg/kg QW sc plus Rebetol® 800-1400 mg per os divided in 2 daily doses for additional 12 weeks beyond standard treatment with 24 weeks follow-up

[figure not shown]

### 3.2 Endpoints

Primary endpoint is

- Reduction of Relapse rate (HCV-RNA positive in serum by a standard HCV-PCR with a detection limit of at least 15 IU/ml) 24 weeks after the end of treatment and thus improvement of sustained virological response rates (SVR)

Secondary endpoints are

- Virological response rates (HCV-RNA negative in serum by a standard HCV-PCR with a detection limit of at least 15 IU/ml) at the end of therapy
- Biochemical responses as determined by ALT and AST levels at the end of treatment and at the end of follow up.
- Severity and frequency of adverse events (AE)
- Analysis of quality of life (with questionnaire SF-36)

### **3.3 Assignment to Treatment Groups**

150 patients with chronic hepatitis C virus infection of the genotypes 2 and 3 shall be enrolled. Patients will be randomized 1:1 in group A (75 patients) and B (75 patients). Stratification factors will be sex, age, genotype, cirrhosis, and the HCV RNA level > 600.000 IU/ml before the ongoing therapy.

## **4 STUDY POPULATION**

### **4.1 Target Population**

The target population is male and female with HCV-genotype 2 or 3 chronic hepatitis c virus infection, ≥ 18 years of age.

### **4.2 Inclusion criteria**

For inclusion into the study, a patient must satisfy the following criteria:

1. Male or female patients with HCV-genotype 2/3 chronic hepatitis C documented by detectable plasma HCV RNA (> 15 IU/mL) and positivity of anti-HCV antibodies
2. Age ≥ 18 years
3. Compensated liver disease (Child-Pugh Grade A clinical classification)
4. Negative urine or blood pregnancy test (one of the both; for women of childbearing potential) documented within the 24-hour period prior to the first dose of study drug. Additionally, all fertile males and females must be using two forms of effective contraception during treatment and during the 7 months after treatment end. This includes using birth control pills (no interaction with investigational drugs), IUDs, condoms, diaphragms, or implants, being surgically sterilized, or being in a post-menopausal state. At least one contraception method must be of barrier method
5. Ongoing treatment with 1.5 µg/kg Peg-Interferon alpha-2b (PegIntron®) and > 10.6 mg/kg ribavirin (Rebetol®)
6. No rapid virological response (HCV-RNA positive after week 4 of the ongoing therapy)
7. Willingness to give written informed consent and willingness to participate to and to comply with the study protocol

### **4.3 Exclusion criteria**

Patients with any of the following criteria will be excluded from the study:

1. Women with ongoing pregnancy or breast feeding
2. Male partners of women who are pregnant
3. Coinfection with HIV or HBV
4. History or other evidence of a medical condition associated with chronic liver disease other than HCV associated (e.g., hemochromatosis, autoimmune hepatitis, alcoholic liver disease, toxin exposures)
5. History or other evidence of bleeding from esophageal varices or other conditions consistent with decompensated liver disease
6. Patients with liver cirrhosis with a lesion suspicious for hepatic malignancy on the screening
7. Absolute neutrophil count (ANC) <750 cells/mm^3 at screening
8. Platelet count <50,000 cells/mm^3 at screening
9. Hb <10 g/dl at screening

10. Dose modification of Peg-Interferon alpha-2b (PegIntron®) or ribavirin (Rebetol®) during the first 4 weeks of the ongoing therapy
11. Interferon alpha or ribavirin therapy at any time point before the actual ongoing treatment
12. Less than 80% adherence to treatment of the ongoing treatment until randomization (week 20-22 of ongoing treatment)
13. Serum creatinine level >1.5 times the upper limit of normal at screening
14. History of severe psychiatric disease, especially depression (ICD 10 codes F30–F33). Severe psychiatric disease is defined as treatment with an antidepressant medication or a major tranquilizer at therapeutic doses for major depression or psychosis, respectively, for at least 3 months at any previous time. Patients are excluded if any history of suicidal attempts is evident. If hospitalization for psychiatric disease, or a period of disability due to a psychiatric disease are documented, psychiatric consultation is mandatory. Patients with a mild or moderate psychiatric disease (ICD 10 codes F32.0, F32.1, F33.0, F33.1) are only allowed to be included into the trial if a regular monitoring by a psychiatrist is performed during the trial
15. History of a severe seizure disorder or current anticonvulsant use
16. History of immunologically mediated disease (e.g., inflammatory bowel disease, idiopathic thrombocytopenic purpura, lupus erythematosus, autoimmune hemolytic anemia, scleroderma, severe psoriasis, rheumatoid arthritis)
17. History or any other evidence of autoimmune diseases
18. History or other evidence of chronic pulmonary disease associated with functional limitation
19. History of significant cardiac disease that could be worsened by acute anemia (e.g. NYHA Functional Class III or IV, myocardial infarction within 6 months prior to treatment with Peg-Interferon/ribavirin therapy, ventricular tachyarrhythmias requiring ongoing treatment, unstable angina)
20. Evidence of thyroid disease that is poorly controlled on prescribed medications
21. Evidence of severe retinopathy (e.g. CMV retinitis, macular degeneration)
22. History of major organ transplantation with an existing functional graft
23. History or other evidence of severe illness, malignancy or any other conditions which would make the patient, in the opinion of the investigator, unsuitable for the study
24. History of any systemic anti-neoplastic or immunomodulatory treatment (including supraphysiologic doses of steroids and radiation) 6 months prior to the first dose of study drug or the expectation that such treatment will be needed at any time during the study
25. Patients with evidence for tuberculosis
26. Drug abuse within 6 months prior to the first dose of study drug and excessive alcohol consumption. Patients on methadone/polamidone/buprenorphine programs are not excluded
27. Any investigational drug and/or participation in another clinical study prior 6 months to the actual ongoing antiviral treatment
28. Limited contractual capability

## **5 SCHEDULE OF ASSESSMENTS AND PROCEDURES**

All laboratory testing will be performed locally at each site. Each investigator is responsible to submit appropriate laboratory certificates and all ranges of normal values to the HEP-NET study coordinator.

Only laboratories can be involved taking part in quality control programs regularly.

HCV-RNA will be analyzed in a central lab at Hannover Medical School, Clinic for Gastroenterology, Hepatology, and Endocrinology, [name], [name], [name], [name]; [contact]).

### 5.1 Study Procedures / Assessments

Table 2: Schedule of assessments and procedures

| Assessment                   | Screening | Study Treatment Week (TW) 0 | Study Treatment Week (TW) 4,8,12,16*,20*,24* (*only group A) | Follow-up (FU) 4,12,24 |
|------------------------------|-----------|-----------------------------|--------------------------------------------------------------|------------------------|
| Informed consent             | X         |                             |                                                              |                        |
| Medical & Medication History | X         |                             |                                                              |                        |
| Physical Examination         | X         |                             |                                                              |                        |
| Vital Signs                  | X         | X                           | X                                                            | X                      |
| Adverse Events               |           | X                           | X                                                            | X                      |
| Weight                       | X         | X                           | X                                                            | X                      |
| ECG                          | X         |                             |                                                              |                        |
| HCV-RNA                      | X         | X                           | Only end of treatment                                        | X                      |
| Haematology                  | X         | X                           | X                                                            | X                      |
| Chemistry                    | X         | X                           | X                                                            | X                      |
| TSH                          | X         |                             | Only TW 12, 24                                               | Only FU 24             |
| Pregnancy Test               | X         | X                           | X                                                            | X                      |
| Questionnaire SF-36          |           | X                           | Only TW 12, 24                                               | Only FU 12, 24         |

Vital Signs: Blood pressure, Heart Rate

Haematology: haemoglobin, RBC, WBC, platelets, coagulation (INR or quick)

Chemistry: creatinine, ALT, AST, Bilirubin, gGT, glucose

A total of approximately 15 ml of blood will be needed at each visit.

### 5.2 Screening Examination and Eligibility Screening Form

A screening examination should be performed between week 12 and week 22 of ongoing treatment before randomization and study entry (= week -12 and week -2 of study).

During the screening, candidates for the study will be fully informed about the nature of the study and possible benefits and risks, and will receive a copy of the patient information and the informed consent form for review. Candidates must read the patient information and sign the consent form if the investigators have answered all questions to the candidate's satisfaction. Further procedures can begin only after the consent form has been signed. One copy of the signed consent form will be retained by the investigator and a second copy will be given to the candidate.

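### Open-label randomisation at week 20–22 precedes TW0 by 2–4 weeks, so one inclusion criterion cannot yet be verified and the only baseline SF-36 is probably completed with the arm already known

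*Protocol*

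**What the plan says.** The timing has to be assembled from several places in the protocol.

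- **Design (3.1):** "This is a German open label multi center randomized phase IV trial". Group A receives 24 and Group B 12 additional weeks of the same two drugs at the same doses.
- **Screening (5.2):** "A screening examination should be performed between week 12 and week 22 of ongoing treatment before randomization and study entry", equated there with "week -12 and week -2 of study".
- **Randomisation:** its time appears only in the adherence criterion, exclusion 12 of section 4.3: "until randomization (week 20-22 of ongoing treatment". Section 3.3, on assignment to groups, gives no time.
- **Pregnancy test (4.2, item 4):** for women of childbearing potential, a negative test "documented within the 24-hour period prior to the first dose of study drug".
- **Laboratory exclusions (4.3, items 7, 8, 9 and 13):** neutrophils, platelets, haemoglobin and creatinine are each tied to screening, for example "Hb <10 g/dl at screening".
- **Schedule (5.1, Table 2):** there is no visit between screening and TW0. The row "Questionnaire SF-36" starts at TW0, as does the adverse event row. Vital signs, weight, HCV-RNA, haematology, chemistry and the pregnancy test are done at both screening and TW0.
- **Analysis set (8.1):** the ITT population is defined as randomised patients with at least one PEG-interferon injection.

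**The concern.** Randomisation should come after eligibility is settled and the baseline is taken, and as close as possible to the point where the arms can differ. Here it comes earlier than all three.

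When a woman of childbearing potential is randomised, one inclusion criterion is still open. Quality of life is a listed secondary endpoint, yet its baseline is a self-report that may be given by a patient who has known for weeks whether 12 or 24 more weeks of interferon lie ahead. Adverse event recording starts under the same condition.

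The gap also allows withdrawal after allocation but before study treatment. Reluctance to face the longer course could make that withdrawal differ between arms. The ITT definition may then remove those patients. It also does not say whether injections of the ongoing standard treatment, given between randomisation and TW0, count as the qualifying injection.

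**Working it through.** **Timeline.** Inputs are sections 5.2 and 4.3 (item 12).

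- Position of TW0: week 12 is study week −12, and 12 + 12 = 24; week 22 is study week −2, and 22 + 2 = 24. Both give week 24. Section 7.6 agrees, describing 24 weeks of treatment before study entry.
- Randomisation to TW0: 24 − 22 = 2 weeks to 24 − 20 = 4 weeks.
- Oldest permitted screening value at randomisation: 20 − 12 = 8 weeks if randomised at week 20, and 22 − 12 = 10 weeks if randomised at week 22.
- Oldest permitted screening value at TW0: 24 − 12 = 12 weeks.

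**Pregnancy criterion against randomisation.** The first dose of study drug is not defined. Table 2 schedules a pregnancy test at TW0, which supports reading it as the TW0 dose. A test within 24 hours of that dose cannot exist 2 to 4 weeks earlier.

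**Which baselines are exposed.** SF-36 and adverse events have no value before TW0. The other TW0 measures also have a screening value, and section 5 sends HCV-RNA to a central laboratory, so knowledge of the arm has little route to distort them.

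**Is early randomisation needed?** Section 3.1 gives both groups the same treatment up to TW12. Nothing that depends on the arm happens between week 20 and TW12, and the protocol states no reason for allocating early.

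**The plan's power figures, and what loss in the gap could do.** Inputs from section 8.2: 75 per group, one-sided 5%, SVR 70% (historical), 95% (A) and 85% (B).

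- B against 70%, exact binomial: success at 60/75 or more, actual alpha 0.0353, power 91.1% (93.7% by normal approximation). The plan says at least 90%.
- A against 70%: above 99.99%. The plan says nearly 100%.
- A against B, with continuity correction: power = Φ{[d − 1/n − 1.645·√(2p̄(1−p̄)/n)] / √[(pA(1−pA) + pB(1−pB))/n]}. With d = 0.10, n = 75 and p̄ = 0.90 this is Φ{[0.1000 − 0.0133 − 0.0806] / 0.0483} = 55.0%. The plan says 55%.

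All three reproduce. The protocol gives no rate of loss between randomisation and TW0, so the following losses are assumptions:

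| Loss before TW0 (assumed) | n per group | A vs B | B vs 70% (exact) |
|---|---|---|---|
| 0% | 75 | 55.0% | 91.1% |
| 5% | 71 | 52.5% | 89.6% |
| 10% | 67 | 49.9% | 87.9% |

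A against 70% stays near 100% throughout. Exactly 75 per group are to be randomised, so there is no reserve for such loss.

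**The case against.** Much can be said for the protocol, and several stronger readings fail.

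- **Breached laboratory limits.** A reader might infer that patients are randomised in breach of the trial's own limits. They are not: items 7, 8, 9 and 13 refer to screening, and a patient who met them then is eligible as written. Haematology and chemistry are repeated at TW0, and Table 4 in section 7.5 covers later changes. Ten and twelve weeks are the worst case the windows permit, not the typical case.
- **The primary result.** A reader might infer that a few wrongly included patients could tip the primary test, since 60/75 passes (0.0353) and 59/75 does not (0.0620). The documents give no rate of such patients and no reason why they would fail to respond. Under the plan's own 95%, Group A expects 0.95 × 75 = 71.25 successes, about 11 above the bar.
- **SF-36 adjustment.** A reader might infer that the quality-of-life comparison is adjusted for the TW0 score. Section 8.1 describes only exploratory comparisons by standard tests and mentions no adjustment. The later SF-36 reports are open label whatever happens at TW0; moving randomisation cleans the baseline and nothing after it.
- **Pregnancy test.** The point concerns only women of childbearing potential. A test is also done at screening, and the 24-hour test can be seen as a pre-dose check that TW0 provides.
- **Disclosure.** The protocol does not say when the arm is disclosed. That it is known by TW0 is an inference from the open design and the gap.

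These objections limit the size of the point. They leave the order of events as it is: allocation first, then the last eligibility check, the only SF-36 baseline and the first study injection.

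**Conclusion.** The point holds as a defect of sequence that should be corrected. Randomisation precedes TW0 by 2 to 4 weeks. One inclusion criterion therefore stays open at allocation for women of childbearing potential, SF-36 and adverse events have no record from before allocation, and the ITT set may lose patients who leave in the gap. Laboratory eligibility values may be up to 10 weeks old at randomisation and 12 weeks old at TW0.

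This rests on three readings: that the parenthesis in exclusion 12 does fix the time of randomisation, that the first study dose is the TW0 dose, and that the arm is not concealed until TW0. The documents support the first two, and nothing in them contradicts the third.

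No effect on the primary SVR comparison is shown. The damage is to the interpretation of quality of life and adverse events and to the completeness of the randomised comparison of A with B. That comparison's planned power of 55% would fall to about 50% only if 10% were lost in the gap, which is an assumption.

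**What to change.** Randomise at TW0 (week 24), after the pregnancy test, blood draw and SF-36 already scheduled for that visit. Consent and screening stay where they are. Because the arms are treated alike until TW12, study treatment can start at once and no patient's treatment changes. The first injection after randomisation is then a study injection, which also removes the doubt about background injections in the ITT definition.

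The text needs these changes:

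- State the time of randomisation in section 3.3, and align the parenthesis in exclusion 12 and the wording of section 5.2 with it.
- Add a note to Table 2 that the TW0 assessments precede randomisation.
- Have the sponsor reconcile the laboratory criteria tied to screening with the new time of randomisation. No limit or window is proposed here.

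The cost is one amendment; moving the randomisation date adds no visit or test to Table 2. A few screened patients will be found ineligible at TW0 and will not be randomised. If early allocation serves a practical purpose such as drug supply, the protocol should say so; supply up to TW12 does not depend on the arm.
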